### Process and health economic evaluation

As part of the trial, a process evaluation will be undertaken to determine the feasibility, fidelity, acceptability and reach of the intervention in these novel contexts. We will also record the key costs of the intervention and assess the feasibility of measuring outcomes including health-related healthcare resource use.

A process evaluation framework will be developed at the start of the study and will cover the:

*Feasibility and acceptability of intervention*: for example, the proportion of nominated peer supporters who agreed to participate, the acceptability of the intervention to teachers and parents.*Feasibility and acceptability of the study processes* to peer supporters, non-peer supporters, teachers and parents: that is, recruitment, retention and data collection.*Reach of the intervention*: we will assess the level of exposure to the intervention via the social network questionnaire. We will also explore this in the interviews/focus group.*Fidelity of implementation*: we will assess whether the key components of the ASSIST intervention were delivered, and what components, if any, were not delivered with fidelity.*Contextual factors and programme theory*: we will assess contextual factors at individual-level, school-level and country-level and apply these to a refined programme theory. We will also explore the wider policy environment.*Impact* of the study/intervention on peer supporters, including changes in the confidence, self-esteem or social networks of the peer supporters.*Contamination*: that is, where students in control schools hear about ASSIST or receive elements of ASSIST (eg, via social media) as well as what control and intervention schools are delivering to students regarding smoking prevention.

Process data will be gathered using multiple methods including questionnaires, observations, interviews and focus groups as well as social network data. The follow-up questionnaire will include items for: non-peer supporters to assess awareness, understandings and opinions of the intervention; and for peer supporters, we have a short questionnaire which will assess their understandings and opinions of the intervention. We will also ask peer supporters about how much they engaged with the intervention, for example, number of conversations, messages posted, etc. Students in all schools will also be asked about conversations about smoking and key smoking-related knowledge items in the questionnaire.

#### Observations

Observations of peer supporter nomination and recruitment, peer supporter training and peer supporter follow-up sessions will be conducted by research staff. Peer supporter training will be filmed for Evidence-to-Impact (the training provider) to quality assure intervention delivery, and this data will be used for the intervention fidelity assessment.

#### Qualitative data

Qualitative interviews and focus groups will explore views and experiences of feasibility, acceptability, adaptability to the country context, barriers, facilitators and reach of the intervention and its components and potential adaptations. Comparison between countries and within and across different participant groups involved in the intervention, such as trainers’ views and peer supporters’ views, will be enabled through a Framework Analysis approach.

In intervention schools, we will aim for: interviews with two staff members per school (n=12), three parents per school (n=18) and three student focus groups per school (two with peer supporters, one with non-peer supporters). Peer supporter focus groups will have a minimum of six students per group (n=72 peer supporters per country). Non-peer supporter focus groups will have a minimum of 8 per group (n=48). We may also conduct paired student interviews if focus groups prove challenging to organise. In control schools, we will interview one staff member per school (n=4). We will also interview up to six ASSIST trainers per country and four policy makers per country. See online supplemental file 5 for the interview guides.

#### Social network data

We will collect sociocentric data on friendship networks at baseline and follow-up. We will use this data to investigate the patterns of social structure within each school and assess the network position of peer supporters (eg, are they well connected or central in the network?). Data will be collected about friendships within the year group, as well as out-of-school friends.

#### Web/app analytics

We will collect website usage data for both peer supporters and non-peer supporters using Google Analytics to assess online engagement with the intervention.

#### Health economics data

We will develop a data collection form to pilot collection of the key resources used in the intervention implementation and maintenance. We will assess the completeness of the data collected, highlighting any missing data.

#### Sample size and power

The study does not aim, and is not designed, to identify a precise estimate of the effectiveness of the intervention within any one country or across countries. To do so would require longer follow-up than the 7 months, we propose and a sample size in the approximate magnitude (c. 60 schools and 12 000 students) of the original ASSIST trial.^33 34^

#### Quantitative analysis

A detailed Statistical Analysis Plan has been drafted and will be finalised before the data collection is complete.

##### Baseline characteristics

Baseline characteristics will be summarised overall and by country and intervention group, with statistical comparison of baseline data being made between countries. These baseline characteristics include sociodemographic information such as age, gender and ethnicity, as well as information related to smoking that will be analysed as secondary outcomes during the analyses.

##### Feasibility outcomes

These will be the primary focus of the analysis. The assessment of whether and how feasible it is to conduct a full-scale effectiveness evaluation of an adapted version of the ASSIST intervention in Indonesia and the Philippines will be done through descriptive statistics for each country for each of the quantitative progression criteria.

##### Efficacy outcomes

To identify effect estimates, a cluster-level analysis will be undertaken with school-level strata, baseline weekly smoking and gender included as covariates. Country will be included as a fixed effect in a model combining data from both countries, and country-specific models will also be estimated. Results will be reported in the form of risk ratios and risk differences, with corresponding 95% CIs. The primary analysis will be of risk ratios in separate country-specific models.

The primary effectiveness outcome is self-reported weekly smoking. Secondary outcomes will include student-level variables such as smoking behaviour (own and that of friends and family); e-cig use and vaping and other forms of nicotine use; smoking-related attitudes and knowledge; smoking norms; self-esteem; spillover effects on parents, etc, and self-efficacy. These analyses will be exploratory as the study is not powered to identify precise estimates of effect.

Missing data will not be imputed, unless more than 20% of cases are lost due to missing data for the primary outcome at follow-up, in which case multiple imputation will be performed. Sensitivity analysis will also be carried out in the event of multiple imputation to compare the effect of missing data on the primary outcome and compare alternative imputation methods.

##### Social network analysis

Social network analysis will be used to assess intervention acceptability and feasibility—that is, whether peer supporters reached most of the year group. Analyses will identify the percentage of friendship clusters that have at least one peer supporter within them. Clustering algorithms (eg, Girvan-Newman) will be used for these analyses.

Social network analysis will also be used in exploratory analyses. Descriptive analyses will measure the structure of each network, such as how densely connected the friendship clusters are and compare these across countries. The tendency for students to be friends with peers who share their smoking habits will be tested, as well as the extent to which smokers are popular in the network. Longitudinal network models (eg, Stochastic Actor-Oriented Models) will measure changes in friendships and smoking over the course of the intervention. We will also measure the reach of peer supporters to ‘at-risk’ students (students who smoke), to determine if the supporters reached those most in need of the intervention.

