### Trial participants

Ten secondary schools will be recruited in each country. Depending on the availability of relevant data, we will attempt to specifically target schools in areas of lower socioeconomic status and with high smoking rates. Each year group size will be between 100 and 500 students (mean c.333), so there will be approximately 4000 students in intervention schools and 2666 students in control schools overall. ASSIST is a whole school year-group intervention, thus all students in the target school year (aged 13–14 years) in each country will be potentially eligible to participate in the intervention and research. Students in the target school year who are outside of the 13–14 age group will not be excluded, as students in the target class in Indonesia may be age 15 by public school regulation, and some students in the Philippines may have had to pause or delay their studies due to socioeconomic hardship or challenges in completing their schoolwork.

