### The intervention group

In the initial stages of the study, we will conduct stakeholder work with policymakers, principals, teachers and students to refine the intervention to allow tailoring to the country contexts. We will also recruit trainers who will be trained to deliver the intervention. The training will be piloted in one school, and the trainers will receive feedback.

Schools in the intervention arm will receive the ASSIST intervention in addition to the usual school education on smoking. Peer supporters will be recruited from among the target year group who have been voted as ‘most influential’ by their year group via a short questionnaire. Around 18% of the students who receive the most nominations, stratified by gender, will be invited to a recruitment meeting. Those who choose to take on the role will attend a 2 day training course run by the trainers. Over a defined period of 10 weeks, peer supporters will use social media and face-to-face interaction to disseminate messages aimed at preventing smoking. They will encourage their friends/peers in their year group not to take up smoking. They will be supported—through regular meetings and via social media—by the professionals who trained them. They will also have access to ASSIST global resources (assistglobal.net which is adapted for each country and a moderated forum) for further support. Although only about 18% of the cohort will be trained to be peer supporters, the effect of the programme is likely to be seen across the year group as the remaining students will receive the intervention via informal interactions initiated by the peer supporters.

The ASSIST global programme theory is summarised in the logic model below (figures3  4) and was adapted from the STASH study.^25^

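### The cluster-based reach statistic shows where supporters sit, not whether most students were reached, so a high value needs a student-level measure and a chance reference beside it

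*Protocol article*

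**What the plan says.** The protocol article, under Social network analysis, sets the question: "Social network analysis will be used to assess intervention acceptability and feasibility—that is, whether peer supporters reached most of the year group". The next sentence gives the statistic: "Analyses will identify the percentage of friendship clusters that have at least one peer supporter within them". On method it adds only "Clustering algorithms (eg, Girvan-Newman) will be used for these analyses". It states no expected cluster size, no rule for where the algorithm is cut and no value expected by chance.

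The supporter share comes from The intervention group: "Around 18% of the students who receive the most nominations, stratified by gender, will be invited to a recruitment meeting", and later "Although only about 18% of the cohort will be trained to be peer supporters". Trial participants gives the network size: "Each year group size will be between 100 and 500 students (mean c.333".

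Other information on reach is planned elsewhere. Process and health economic evaluation plans to assess exposure through the social network questionnaire and to explore it in interviews and focus groups. The same section puts awareness items to non-supporters, asks supporters how much they engaged, and asks students in all schools about conversations on smoking. Qualitative data and Web/app analytics add further material.

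**The concern.** The question is about students: did most of them come within reach? The statistic is about clusters: does each hold at least one supporter? The two can part in three ways.

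- **Unit.** One supporter in a cluster of 40 scores the same as one in a clique of 4.
- **Presence against contact.** The figure needs only the friendship network and the list of supporters. It would be unchanged if no supporter had held a single conversation.
- **Cluster size.** The larger the clusters the algorithm returns, the more likely each is to hold a supporter, whatever the supporters did. The algorithm is named only as an example, so this is left open.

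Reach is one of the listed secondary objectives, and this section presents the network result as evidence on acceptability and feasibility. At stake is a favourable statement about reach that rests on a figure which would be fairly high anyway.

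**Working it through.** The protocol states no value for this statistic, so there is none to reproduce. The check asks what value to expect if supporters were scattered at random.

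**Inputs.** Supporter share p = 0.18 (The intervention group). Year group N = 333 on average, range 100 to 500 (Trial participants), so about 0.18 × 333 = 60 supporters. Cluster size m is not given; values from 3 to 20 are assumed.

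**Equal clusters.** The chance that a cluster of m students holds at least one supporter is 1 − (1 − p)^m.

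| m | 1 − 0.82^m |
|---|---|
| 3 | 45% |
| 4 | 55% |
| 5 | 63% |
| 10 | 86% |
| 15 | 95% |
| 20 | 98% |

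Coverage passes one half at m = ln(0.5)/ln(0.82) = 3.5, so from clusters of 4 upwards.

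**Finite year group.** The exact form 1 − C(N−K, m)/C(N, m), with N = 333 and K = 60, gives 63%, 87%, 95% and 98% for m = 5, 10, 15 and 20. Year groups of 100 and 500 give nearly the same.

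**Fewer supporters.** At m = 10, p = 0.15 gives 80% and p = 0.10 gives 65%.

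**Unequal clusters.** In a simulation with N = 333, 60 supporters placed at random and cluster sizes drawn from a gamma distribution (shape 2), mean coverage was:

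| Mean size | Clusters covered | Students in covered clusters |
|---|---|---|
| 5 | 57% | 69% |
| 10 | 75% | 87% |
| 15 | 84% | 93% |
| 20 | 89% | 96% |
| 30 | 93% | 98% |

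Varying sizes lower the chance figure. They also separate the share of clusters from the share of students. Under random placement the cluster share is the smaller, because large clusters are the more likely to be covered. With non-random placement the gap can go either way. Take one cluster of 40 and one of 4, with only one of them covered. The cluster figure is 50% in both cases, but the student share is 40/44 = 91% or 4/44 = 9%.

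**Presence against contact.** Suppose a covered cluster has one supporter with 5 friends in it (an assumption). The share of the other members directly tied to that supporter is 5/9 = 56% in a cluster of 10, 5/19 = 26% in one of 20 and 5/29 = 17% in one of 30. All three clusters count as fully covered.

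**The case against.** The strongest reply is that this is one descriptive statistic among several. Exposure, awareness and conversation items, focus groups and web usage all bear on reach, so cluster coverage is not the only measure. That stands. However, the Social network analysis section does not tie its own conclusion to those items.

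A second reply is that coverage is real however it arose: if supporters sit in nearly every cluster, it does not matter that random choice would have done the same. That too stands as far as it goes. The chance reference does not make the coverage false; it shows how little a high figure adds.

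Third, the direct-tie measure proposed here also rises by chance. A student with d ties has at least one to a supporter with probability of about 1 − 0.82^d, which is 63% at d = 5 and 86% at d = 10. This is correct, and it is why the random reference and the student-reported items belong with it.

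Some stronger readings are tempting but not supported:

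- *The measure passes whatever happens.* Cluster size is unknown, varying sizes lower the chance value, and nominated supporters may bunch in a few clusters. A low result is possible and would be informative.
- *Students outside any cluster drop out.* The protocol does not say so. Girvan-Newman, the named example, partitions all students, so an isolated student becomes a cluster of one.
- *It feeds a progression threshold.* The progression criteria are in a supplementary table that is not shown, and nothing visible links this statistic to them.
- *The at-risk group must be redefined.* The protocol defines it as "students who smoke), to determine if the supporters reached those most in need of the intervention", while supporters' task is described as "They will encourage their friends/peers in their year group not to take up smoking". But this is a separate exploratory measure beside whole-year-group reach, which includes non-smokers. Another definition would be a preference, not a correction.

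**Conclusion.** The point holds as a limit on interpretation. Cluster coverage is a necessary check on reach, not a sufficient one. With 18% supporters placed at random it is already 63% to 95% for equal clusters of 5 to 15, and about 57% to 84% for the same mean sizes when sizes vary. It exceeds one half from equal clusters of 4 upwards. These figures rest on assumed cluster sizes, on random placement as the reference and, for the unequal case, on one assumed size distribution; a smaller trained share lowers them.

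The objections about unit and contact do not depend on cluster size. A high percentage therefore cannot by itself support the statement that most of the year group was reached, whereas a low one would count against it.

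**What to change.** In the Social network analysis section, or in the analysis plan before it is finalised:

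1. For each school, report the percentage of non-supporters who have a direct friendship tie to a trained supporter. As a minimum, report the percentage of students who are in covered clusters.
2. Beside it, give the value obtained when the same number of supporters of each gender is drawn at random, repeatedly, from the same network.
3. Base any conclusion that most of the year group was reached on the student-reported exposure, awareness and conversation items already planned under Process and health economic evaluation.
4. Keep the cluster percentage as a description of structure.

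The network and questionnaire data are already to be collected. The cost is a change of wording, a modest amount of extra analysis, and possibly a less favourable reach figure.

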##### Health economic analysis

The health economic analysis aims to evaluate the feasibility and acceptability of acquiring resource utilisation data to estimate the costs associated with the implementation of the ASSIST intervention in Indonesia and the Philippines. The availability of country-level data on the financial implications of smoking will be assessed, including the impact on health services and employment. The feasibility of collecting unit costs from each country will also be evaluated. The following will be estimated: the intervention cost per pupil within each school; the intervention cost in each country and an incremental cost per student not smoking. The feasibility of estimating the impact on the environment resulting from smoking will be assessed using publicly available data combined with the primary outcome of self-reported weekly smoking.

### Qualitative analysis

#### Observations

Video-recordings of student training sessions will be graded against an observation checklist to determine fidelity to the intervention delivery.

#### Interviews and focus groups

A thematic framework method will be used to analyse the qualitative data.^35 36^ This approach typically uses a seven-step process. We will complete the following stages (step 1 is an additional step).

Development of preliminary coding framework aligned to the research questions and informed by research on smoking interventions in adolescents.Transcription and translation of the data.Data familiarisation.Preliminary coding of initial transcriptsRefinement of the coding framework based on the preliminary codingApplication of the coding framework to all the dataCharting and summarising the data into framework matrices. Thematic categories will be largely predetermined, but emergent themes will also be added to the matrices. Each country will have its own matrix to enable within and between country comparisons.Interpretation of the data.

Data will therefore be coded both inductively and deductively.^37^ Around 20% of transcripts from each country will be professionally translated and checked by the local study team before being transferred for review and double coding by the UK team. In addition, country teams will double code an additional 20% of the interviews within their teams.

### Mixed methods

Qualitative and quantitative data are being collected and analysed separately using a convergent parallel approach to mixed-methods research.^38^ The qualitative data, which brings greater depth, are key to understanding the feasibility and acceptability questions. Bringing together both data sets in the interpretation stage provides an opportunity to triangulate the data to offer further insights.

### Patient and public involvement

A Stakeholder Advisory Group (SAG) and a Youth Advisory Group (YAG) have been established in each country. The SAGs include 5–7 members who are public health/education officials, school principals/teachers, academics, parents; and the YAGs are made up of 5–6 students of the same target age group from schools that are not involved in the study.

The SAG and YAG will contribute to the design of the feasibility trial, including adaptations to the intervention and study materials (eg, study questionnaire, training activities in the manual and relevant resources such as posters), as relevant to the local culture and context. The SAG and YAG will be involved throughout the duration of the study and dissemination of findings. The process of deciding on adaptations will involve consultation with partners and our advisory groups. The trial team will make final decisions on adaptations considering both what is feasible to implement and also what can be adapted while retaining the key intervention mechanisms described in the programme theory.

## Trial management

The TMG comprising the Principal Investigator, coinvestigators and Project Manager will meet regularly and review progress and important protocol modifications. The TMG will report to the independent TSC which consists of a chair, a statistician and other experts, and will operate according to Medical Research Council guidance (https://www.ukri.org/publications/mrc-short-guide-to-trial-steering-committees/). Routine reports reviewed by the TSC will include a summary of adverse events if there are any. The TSC will cover the functions of the Data Monitoring and Ethics Committee (DMEC) due to the low-risk nature of this study and the lack of a need for unblinded/interim analysis.

